**Methods/design:**

The current study is a randomised single-blind, parallel-group clinical trial, with a one and a half year follow-up, conducted in eight Primary Health Care Centres located in the city of Barcelona. Inclusion criteria are to be aged 65 years or older with positive frailty screening, timed get-up-and-go test between 10 to 30 seconds, and Cognition Mini-Exam (MEC-35) of Lobo greater than or equal to 18. A total of 352 patients have been equally divided into two groups: intervention and control. Sample size calculated to detect a 0.5 unit difference in the Short Physical Performance Battery (Common SD: 1.42, 20% lost to follow-up). In the intervention group three different actions on frailty dimensions: rehabilitative therapy plus intake of hyperproteic nutritional shakes, memory workshop, and medication review are applied to sets of 16 patients. Participants in both intervention and control groups receive recommendations on nutrition, healthy lifestyles, and home risks.

Evaluations are blinded and conducted at 0, 3, and 18 months. Intention to treat analyses will be performed. Multivariate analysis will be carried out to assess time changes of dependent variables.

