### Sample size calculation

Sample size has been calculated to detect minimal significant effects on the variable of physical performance (SPPB): Accepting an alpha risk of 0.05 and a beta risk of 0.20 in a bilateral contrast, 318 individuals are required in order to detect a difference equal to or greater than 0.5 units in the SPPB[49, 50]. The common standard deviation has been taken to be 1.42. A drop-out rate of 20% is anticipated. Finally, 352 subjects have been included (n = 176 IG and n = 176 CG).

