### Statistics

Intention to treat analyses will be performed. Baseline characteristics will be compared between groups by independent t tests and Chi-square tests. Outcome variables will be calculated for each individual and time point (difference between the result of SPPB, muscle strength, and other frailty variables in each time point and the initial value), and 95% confidence intervals for the differences between groups will be calculated. Data will be analysed using repeated measures analysis of variance (ANOVA) consisting of intervention and control groups and time (baseline, post-intervention, follow-up).

Also, for longitudinal adverse outcome measures (disability, home care inclusion, institutionalization or death), survival analyses using Cox’s regression models will be applied. The statistical significance level will be set at p <0.05.

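### The three-visit repeated measures ANOVA does not by itself deliver the declared intention-to-treat analysis, and the text does not say whether it or the per-visit change analysis governs

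*Protocol article*

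**What the plan says.** The Statistics section opens with the analysis principle: "Intention to treat analyses will be performed". It then describes two treatments of the continuous outcomes. The first takes each participant's change from baseline at each time point and gives 95% confidence intervals for the difference between groups. The second is the longitudinal model: "Data will be analysed using repeated measures analysis of variance (ANOVA) consisting of intervention and control groups and time (baseline, post-intervention, follow-up". The section names no imputation method and no mixed model. It does not say that only completers are analysed. Adverse outcomes, including institutionalization and death, go to Cox regression.

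The visit schedule is in the abstract: "Evaluations are blinded and conducted at 0, 3, and 18 months". The Study design section places the comparison of changes from baseline at month 3, the end of the intervention, and uses month 18 to see whether effects last. The Sample size calculation section says: "A drop-out rate of 20% is anticipated" and "Finally, 352 subjects have been included (n = 176 IG and n = 176 CG".

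**The concern.** A conventional repeated measures ANOVA needs a complete row for each participant. Someone measured at baseline and month 3 who dies, moves to a nursing home or withdraws before month 18 contributes nothing to any contrast from that model, including the month-3 contrast. The month-3 result from the ANOVA would then be conditioned on attending a visit 15 months later.

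These losses are unlikely to be random. Participants are selected for frailty, and death and institutionalization are themselves outcomes. The Measures section notes that low SPPB scores predict mortality and nursing home admission, so the article itself links the outcome used for the sample size to likely causes of loss. Loss could also differ by arm: the intervention arm attends 12 exercise and 12 memory sessions, while controls are invited to two group sessions. The only stated measure against loss is telephone contact, given in the Discussion.

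At stake are the population that the main estimates describe and the size of the month-3 effect.

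**Working it through.** **Inputs from the protocol article.** The Sample size calculation section gives a two-sided alpha of 0.05, power of 0.80 (beta 0.20), an SD of 1.42 in both groups, 20% drop-out, and 352 included, 176 per arm. Its stated result is: "318 individuals are required in order to detect a difference equal to or greater than 0.5 units in the SPPB".

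**1. Reproduce the planned sample size.**
- n per arm = 2 × [1.42 × (1.96 + 0.8416) / 0.5]² = 126.6, rounded up to 127.
- Total = 2 × 127 = 254.
- Allowing for 20% loss: 254 / 0.8 = 317.5, rounded up to 318.

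This matches the stated figure, so 318 already includes the expected loss.

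**2. Participants who would leave a complete-row ANOVA.**
- Lost: 352 × 0.20 = 70.4, about 70.
- Remaining: 352 × 0.80 = 281.6, about 282 (140.8 per arm).

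**3. Power with completers only** (two-sample normal approximation).
- 0.5 / √(2 × 1.42² / 140.8) = 2.954; power = Φ(2.954 − 1.960) = 84.0%.
- The included 352 would tolerate 1 − 254/352 = 27.8% loss before falling to the required 254.

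**4. Month-3 data at risk.** The article does not give the timing of losses, so only a range can be stated. If every loss comes before month 3, 282 have month-3 data under any method (84% power). If every loss comes after month 3, all 352 have them (91% power), yet the complete-row ANOVA still uses about 282.

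**5. Possible bias at month 3, by simulation.** All settings are assumptions: true month-3 effect 0.50, SD 1.42, correlation 0.6 between visits, and loss before month 18 more likely with a lower month-3 SPPB (logistic slope −1 or −0.5 per SD, the same in both arms). The table gives the difference in change from baseline to month 3 among completers. Repeat runs agree to about 0.01.

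| Loss, control / intervention | Slope −1 | Slope −0.5 |
|---|---|---|
| 25% / 15% | 0.45 | 0.48 |
| 28% / 12% | 0.43 | 0.45 |
| 15% / 25% | 0.54 | 0.53 |
| 20% / 20% | 0.50 | 0.50 |

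Equal loss protects only if the mechanism is also the same in both arms. In a deliberately one-sided run, loss in the intervention arm depended on the month-3 score (slope −1 per SPPB point) and control loss was random at 20%, with about 22% lost overall. Completers then showed 0.64, against 0.50 when everyone seen at month 3 was used.

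**The case against.** The strongest reply is that deletion of incomplete cases is inferred from the name of the method. The article never says it, a repeated measures ANOVA can be run on imputed data, and a condensed article may leave missing-data handling to an analysis plan that is not shown. This stands as far as it goes. A reader might infer that the plan contradicts its intention-to-treat statement or commits to a completers' analysis, and the text does not support either reading. What remains is that the named model, taken alone, does not achieve what is declared; another document would have to replace it or add imputation.

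A second reply is that the per-visit change analysis needs only baseline and the visit in question. This also stands. A reader might infer that month-3 data of later losses are certain to be discarded, but they can be kept in that analysis. The reply leaves open which of the two analyses carries the conclusion when they differ.

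Third, deaths and institutionalizations are not ignored, because Cox regression is planned for them. That is correct, but it does not settle how they affect the SPPB comparison.

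Fourth, a reader might infer that the trial loses its power. It does not, as steps 1 and 3 show.

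Fifth, the bias figures rest on loss rates and mechanisms that the article does not give. That is true; they show sensitivity and are not a forecast.

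Finally, a reader might object that the unequal gaps of 3 and 15 months breach sphericity. Unequal spacing does not in itself do so, and standard corrections exist, so no weight is placed on this.

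**Conclusion.** The point holds in limited form. Without imputation, the ANOVA as named would leave out about 70 of 352 randomised participants at the anticipated loss, and it sits beside a per-visit analysis that may use a different set of participants, with no statement of priority. Power remains about 84%, above the planned 80%.

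The risk is bias, and it is conditional. With loss depending equally on function in both arms but at rates differing by 10 to 16 percentage points, the month-3 effect moves by roughly 0.02 to 0.07 SPPB points against a design difference of 0.5, in either direction. With equal rates and the same mechanism it does not move. It can move further if the mechanism itself differs between arms. This rests on the conventional complete-row form of the ANOVA and on the assumed loss patterns. The matter should be fixed because the better method is readily available and cheap, but the documents do not support calling it a must-fix.

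**What to change.** In the Statistics section, replace the repeated measures ANOVA with a likelihood-based linear mixed model for repeated measures: arm by visit, unstructured covariance, participants analysed in the arm to which they were allocated, and all observed visits used. Keeping baseline in the outcome vector lets participants with no follow-up visit remain in the model. Report the arm contrast separately at month 3 and month 18, and state that these contrasts govern; the per-visit changes with confidence intervals then become descriptive or supportive.

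The mixed model handles loss that is explained by SPPB values already observed. It does not handle loss that depends on unobserved values, and it does not define an SPPB score after death. Add a sensitivity analysis for both, for example one that ranks death below any observed score at month 18 and one that uses delta-adjusted imputation.

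The cost is a few sentences and modest programming. No new data are needed, and the sample size does not change.

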**Table 2 Tab2:** **Measurements at several time points**

	Selection	Baseline		After intervention		18 months	
	All	IG	CG	IG	CG	IG	CG

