**FUNCTIONAL ASSESSMENT**							
Lawton & Brody Scale		x	x			x	x
Barthel Index		x	x			x	x

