**ADVERSE OUTCOMES**							
Falls		x	x			x	x
Fractures		x	x			x	x
Hospital admissions		x	x			x	x
Home care inclusions						x	x
Institutionalizations						x	x
Death						x	x

Fried modified criteria for frailty [3] (three or more of the following criteria have to be present): Unintentional weight loss (3 kg in past 6 months)Self-reported exhaustion (2 questions from CES-D scale)Weakness (5 chair stand-up test, unable)Slow walking speed (more than 10 seconds) evaluated by Timed -up-and-Go test (TGUGT). This is a reliable test for quantifying functional mobility (lower extremities function) and for measuring balance (fall risk). The person may wear their usual footwear and can use any assistive device normally employed. The TGUGT is conducted using a chair with arms, and a seat height of 46 cm, placed upon a flat surface with a line marking the 3m turning point. Subjects are instructed on the word ‘go’, to get up and walk as quickly and as safely as possible to cross the line marked on the path, turn around, walk back to the chair and sit down again. The activity will be timed from the subject’s back leaving the back of the chair to the return of the subject to this same position.Low physical activity measured by the IPAQ Questionnaire[53].Physical performance: 2.1*Short Physical Performance Battery*.The short physical performance battery (SPPB) is a simple standardised objective assessment tool of lower limb function[16] that tests standing balance, ability to repeatedly stand from a sitting position, and habitual gait speed. Each component is scored between 0–4 (total score 0–12) with higher scores indicating better functioning. In community-dwelling older adults, lower SPPB scores predict greater risk of mortality, nursing home admission, hospitalization, and incidence of disability. The SPPB consists of:2.1.1)*Balance test*Participants are asked to hold three increasingly challenging standing positions for 10 seconds each: (1) a side-by-side position, (2) semi-tandem position (the heel of one foot beside the big toe of the other foot), (3) tandem position (the heel of one foot in front of and touching the toes of the other foot).2.1.2)*Repeated chair stands test*This is performed using a straight-backed chair, placed with its back against a wall. Participants are first asked to stand from a sitting position without using their arms. If they are able to perform the task, they are then asked to stand up and sit down five times, as quickly as possible, with arms folded across their chest. The time to complete five stands is recorded and used for future analyses.2.1.3)*Gait speed* (*8 meters walk*)2.1.3)2.2*Functional Reach Test* (FRT).This is a valuable test used to measure standing balance and stretching, detecting balance impairment over time. It can predict the risk of falling. After the examiner explains and shows the FRT, each subject performs 2 trial tests. Functional reach is measured by using a levelled yardstick attached to the wall at the height of the subject’s right acromion. To measure the subject’s reaching distance, an examiner stands 0,5 m away from the measuring tape and records the end reach position, checking that the initial position is correct: subjects stand comfortably with feet approximately shoulder-width apart, just before a line marked on the floor at the same level as the measuring tape beginning (0cm); participants then extend the right arm parallel to the yardstick and, without touching the wall, place the third metacarpal along the measuring tape and have to reach as far forward as they can without losing their balance (end position). Subjects are allowed to balance on their toes; however, touching the wall, stepping while reaching forward, or holding onto their clothing with the left hand invalidate the trial. If invalidated, the trial is repeated with a maximum of 2 tests more to achieve 2 valid trials. All subjects are protected during the test. The best result from the two attempts is recorded.2.3*Unipodal station*The patient is placed in a standing position, arms crossed over the chest, with one leg used for support in an extended position, and the other slightly bent at the knee (there can be no contact between the two legs). Once placed in the correct position (eyes open), the chronometer is activated and then stopped when either the patient moves the foot used as a base or when 30 seconds have passed; two attempts with the same foot are made and the best result recorded.Muscle strength. 3.1*Evaluation of upper extremities strength* is assessed through the measurement of force with a handgrip dynamometer. *Grip strength* is assessed using a portable hand dynamometer (JAMAR®0-90 kg, coding 506320). The participants are seated with their shoulder in a neutral position and their elbow flexed at 90°. Three attempts are performed alternately in each hand; the mean of the three measures is recorded.3.2*Evaluation of lower extremities strength* is assessed through the bilateral measurement of the quadriceps muscle force using a digital dynamometer (Chronojump 1.4.5-1.4.6 Boscosystem® Encoder).Activities of Daily Living (ADL) assessment: 4.1* Lawton & Brody Instrumental Activities of Daily Living scale*[54].This is an instrument assessing independent living skills which are considered more complex than the basic activities of daily living. The instrument is most useful for identifying how a person is functioning at the present and for observing improvement or deterioration over time. There are 8 domains of function measured with the Lawton & Brody scale. Women have been traditionally assessed in all 8 areas of function whilst men have not been asked about the domains of food preparation, housekeeping, and laundering. Individuals are scored according to their highest level of functioning in that category. A summary score ranges from 0 (low function, dependent) to 8 (high function, independent).4.2*Barthel Index of Basic Activities of Daily Living*[55].First developed in 1965, it measures functional disability by quantifying patient performance in 10 activities of daily life. These activities can be grouped according to self-care (feeding, grooming, bathing, dressing, bowel and bladder care, and toilet use) and mobility (ambulation, transfers, and stair climbing). 5-point increments are used in scoring, with a maximal score of 100 indicating that a patient is fully independent in physical functioning, and a lowest score of 0 representing a totally dependent bed-ridden state.Nutritional Assessment:*Mini Nutritional Assessment* MNA®[56]. The MNA consists of four parts: anthropometric measurements, general status, diet information, and subjective assessment. A score of less than 17 points (out of a maximum of 30) is regarded as an indication of malnutrition, 17–23.5 points indicate a risk of malnutrition and >23.5 points indicate that the person is well nourished.Neuropsychologist Performance:The first neuro-psychometric instrument developed in Spain to measure semi-quantitatively cognitive status in clinical neurology was the Barcelona Test (BT). A shortened version of the BT, named Barcelona Test Review[57], is used for neuropsychological area evaluation in our participants and it takes only 20–30 minutes to administer. Tests applied are: 6.1.*Short and Medium*-*Term Verbal Memory* is the capacity to hold a small amount of information in the mind in an active, readily available state for a short period of time (seconds) and medium-term period of time (minutes). For the condition referred to as short term, subjects will be instructed to listen to a little story text, 21-pieced-sentences (elements), read by a blind evaluator; once finished, the patient will be asked to repeat the general content and as many details as he or she can remember; the duration of short-term memory is believed to be in the order of seconds. Then, the participant will be submitted to other cognitive trials to divert attention. After 25 minutes, the subject is directly asked for the story again to evaluate medium-term verbal memory. A commonly cited capacity of short and medium-term is 7±2 elements.6.2.* Animal Naming Test* consists of asking the patient to name as many animals as possible in one minute. A blind evaluator must write down the answers, so they can be checked for duplicate responses (repeated words invalidate one of them). The goal of this test is to score at least 14.6.3.* Evocation of words* beginning with one explicit letter, similar to the previous test, in this case the participant will tell the examiner as many words beginning with “p” as possible in three minutes (repeated words invalidate one of them). All kinds of words are allowed, except plurals or the masculine and feminine of the same word, conjugating verbs, and diminutives. The goal of this test is to score at least 27.6.4.*   Designation of famous people names*, the identification of 30 famous faces and their corresponding name permits an examination of the semantic brain area and can identify a possible clinical syndrome of prosopagnosia. Evaluated by “success”, “failure” or “tip of the tongue (TOT) phenomenon”, goal is 23 success, 3 failure, 4 TOT.6.5.*   Verbal designation of images*. Fourteen pictures of different objects or animals are presented to participants and they have to identify each name as quickly as they can: if subjects guess the name between 0–3 seconds this signifies 3 points, between 3–10 seconds, 2 points, and if takes 10–30 seconds it represents 1 point. If the patient does not recognize the picture-name, it is equivalent to 0 points. Goal of the test is to score 41 points.6.6.*  Verbal abstraction of word pairs*, also called “Similarities – Abstraction”, explores patients’ concept formation ability, as the participant must “extract” the common abstract element that links the two words featured. Through this test the ability to discriminate “concrete thinking “from” abstract thought” can be evaluated. The goal of this test is to score at least 5 of 6 pair of words.Medication 7.1.Number of prescribed drugs.7.2.Number of prescribed benzodiazepines.7.3.Presence of antidepressants (yes/no).7.4.Withdrawal of drugs (yes/no).7.5.Number of drugs retired at the closing date of the study.Quality of life. 12-Item Short-Form Health Survey (SF-12) [58].Adverse Outcomes: Falls, fractures, hospital admissions, institutionalization, inclusion in a Home-Care Program, or death.

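### Cox regression is specified for disability, but the only disability scales described are scheduled at baseline and month 18, so onset falls in one 18-month interval and death before that visit has no stated rule

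*Protocol article*

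**What the plan says.** The Statistics section of the protocol article assigns one method to four outcomes: "for longitudinal adverse outcome measures (disability, home care inclusion, institutionalization or death), survival analyses using" Cox models are to be applied.

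The column groups of Table 2 run "Selection Baseline After intervention 18 months". Under functional assessment, the rows "Barthel Index" and "Lawton & Brody Scale" are ticked in both arms at baseline and at 18 months. Their after-intervention (month 3) columns are empty.

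The Measures text says of the Barthel Index that "it measures functional disability by quantifying patient performance in 10 activities of daily life". It describes the Lawton & Brody scale as a measure of instrumental activities. The article gives no cut-off that turns either score into a disability event, no date of onset and no assessment of function between visits. The telephone contact mentioned in the Discussion is there to limit losses to follow-up.

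Death is listed as a separate adverse outcome. No rule is given for a participant who dies before the month-18 assessment of function.

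**The concern.** A Cox model takes its information from the order in which events occur. If disability is read from Barthel or Lawton & Brody, someone disabled at month 18 became so at an unknown time after baseline. Every event is then recorded at the same nominal time, and any spread in the recorded times reflects appointment dates rather than onset. The article therefore pairs a method that needs event times with a schedule that supplies none for this outcome. Both the method and the schedule are fixed in the article, so this is more than detail left to an analysis plan.

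Two things are at stake. The reported ratio may be close to a risk ratio, a hazard ratio or an odds ratio, depending on a software setting. And participants who die before month 18 have no disability status, in a frail population where disability and death are likely to be related. Delaying the step from frailty to disability is the trial's stated rationale, so readers will give weight to this estimate.

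**Working it through.** **The plan's own figure.** The only planned number is the SPPB sample size. Per arm, 2 × (1.960 + 0.842)² × 1.42² / 0.5² = 126.6, so 127; the total is 254; 254 / 0.80 = 317.5, so 318, as stated. It does not involve disability and does not change here.

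**Inputs for the illustration.** Number per arm: 176 × 0.80 = 140.8, taken as 141 (included number and anticipated drop-out from the sample size section). The disability risks are assumptions, because the article gives none: about 20% versus 12% (28 versus 17 events) and about 40% versus 30% (56 versus 42 events), control versus intervention.

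**All events tied at month 18.** Let d_I and d_C be the events and n the number per arm.
- Breslow: the score equation d_I = (d_I + d_C) × nθ / (n + nθ) solves to θ = (d_I/n) / (d_C/n), the risk ratio. Its model SE for log θ is √(1/d_I + 1/d_C).
- The binomial SE of the log risk ratio is √(1/d_I − 1/n + 1/d_C − 1/n).
- Exact (discrete) ties: the odds ratio.
- Complementary log-log, the grouped-time hazard ratio: ln(1 − d_I/n) / ln(1 − d_C/n).
- Efron ties: fitted numerically.

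| | 28 vs 17 | 56 vs 42 |
|---|---|---|
| Breslow (risk ratio) | 17/28 = 0.607 | 42/56 = 0.750 |
| Efron | 0.582 | 0.703 |
| Complementary log-log | 0.580 | 0.699 |
| Exact (odds ratio) | (17/124)/(28/113) = 0.553 | (42/99)/(56/85) = 0.644 |
| Breslow SE | √(1/17 + 1/28) = 0.307 | √(1/42 + 1/56) = 0.204 |
| Binomial SE | √(0.0945 − 0.0142) = 0.283 | √(0.0417 − 0.0142) = 0.166 |
| Ratio of SEs | 1.08 | 1.23 |

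At exactly 20% versus 12% the Breslow value is 0.12/0.20 = 0.60; the 0.607 above comes from using whole counts.

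The same pattern appears when a true hazard ratio of 0.60 is assumed and the control-arm risk runs from 10% to 40%. Breslow returns 0.615 to 0.660, Efron about 0.60, and exact ties 0.587 falling to 0.538. The spread grows with the risk.

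**Deaths before month 18.** With one event time, a person who died earlier is not in the risk set at that time and contributes nothing to the partial likelihood. A simulation with an assumed 30% disability risk over 18 months and an 18-month death risk of 5%, 10% or 15% gives the share of onsets never observed because death came first. It is about 3%, 6% and 8% if disability does not affect mortality, and about 8%, 15% and 22% if disability triples it.

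**The case against.** The strongest counter-argument is that a fully tied Cox model still gives a usable result. That is correct for Efron ties under proportional hazards. The estimates of 0.582 and 0.703 sit beside the complementary log-log values of 0.580 and 0.699, with nearly equal SEs (0.307 versus 0.308, and 0.204 versus 0.206). The z statistics, −1.76 and −1.73, are almost those of the risk ratio, −1.76 and −1.74. The Breslow SE is too large, which errs on the safe side. A reader might infer that the reported figure could not be a hazard ratio or that its confidence interval must be invalid; the calculations do not support that. What stands is that the answer depends on a setting the Statistics section does not name and, if actual visit dates are used, on booking.

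A reader might also infer that the plan censors deaths as not disabled. The article does not say so. Its list ending in death could even be read as a composite, although the plural (measures) points to separate outcomes. Under a composite, deaths would count as events, but the disability component would still lack an onset date. If disability is modelled alone, the accurate description is a comparison among survivors.

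The link from disability to Barthel or Lawton & Brody is an inference, because no threshold is named as the event. No other disability measure is described, however, so the inference is reasonable.

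Finally, Table 2 also ticks home care inclusion, institutionalization and death only at 18 months. These are events that can be dated from records, so the objection does not automatically carry over, but the article does not say that their dates are collected.

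**Conclusion.** The mismatch holds: Cox regression is named for an outcome whose only described measures place onset somewhere in a single 18-month interval. For the assumed risks the estimate ranges from 0.61 to 0.55 at about 20% versus 12%, and from 0.75 to 0.64 at about 40% versus 30%, by tie handling alone. Part of that range is a difference between estimands (risk ratio, hazard ratio, odds ratio) rather than bias, which is why the plan should name the one it wants. The rule for death before month 18 is not stated, and an ordinary Cox model of disability alone would compare survivors.

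Severity is moderate. Disability is not the outcome on which the trial is sized, so it would be wrong to infer that the SPPB comparison or the sample size of 318 is affected. The conclusion rests on disability being defined from Barthel or Lawton & Brody; the sizes rest on the assumed risks and on 141 assessed per arm.

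**What to change.** In the Statistics section, take disability out of the Cox list and analyse it as a binary month-18 outcome:
- Define the disability event from Barthel and/or Lawton & Brody.
- Estimate a risk ratio by modified Poisson or log-binomial regression, or use a complementary log-log model if a hazard ratio is wanted, adjusted for the baseline Barthel/Lawton score.
- Make disabled or dead by month 18 the main version, with survivors only as a sensitivity analysis.
- Keep Cox regression for home care inclusion, institutionalization and death, provided their dates are recorded, and say that they are. For the first two, treat death as a competing event.

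For disability this changes wording only and needs no additional data. For the other three outcomes the one thing to confirm is that event dates are captured.
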